# **Deaths**

Causality of treatment or trypanosomiasis in the occurrence of deaths during the 2 years follow-up will be categorised as « likely », « unlikely » or « unknown ». Deaths will be analysed as follow:

- Deaths as consequence of trypanosomiasis considered « likely » will be analysed as treatment failure.
- Deaths as consequence of treatment considered « likely » will be analysed as treatment failure.
- Deaths as consequence of treatment and trypanosomiasis considered « unlikely » or « unknown » will be censored for the survival analysis and excluded from the primary end-point analysis.

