**Introduction**

*Trypanosoma brucei gambiense* (*Tbg*) Human African Trypanosomiasis (HAT) is a major public health problem in those areas in which it is currently rife (1). This is all the more so because the political upheavals, which disrupt the operations of the health services and cause population movements encourage the reappearance of historical foci (2,3). This disease, however, is still neglected and it is estimated that the control programmes cover only 10 to 20% of the 50 million people living in endemic regions (2).

HAT, which is consistently fatal in the absence of treatment, respond to a relatively non-toxic therapeutic agent, pentamidine(Pentacarinatâ), if the diagnosis is made at the hemo lymphatic phase (4). In the late stage of the disease, however, when the central nervous system is invaded by the parasite, use of arsenic derivatives such as melarsoprol (Arsobalâ) remains necessary. In about 5% of cases the use of melarsoprol causes iatrogenic encephalopathy, with a fatal outcome in up to 50%.

Eflornithine (difluoromethylornithine or eflornithine, Ornidylâ), for the time being, is the only other drug registered for the treatment of late-stage HAT. The institution of treatment regimens with eflornithine, however, is difficult because of the mode of administration of the product (1 infusion of 2 hours, every 6 hours). Actually, eflornithine is no longer available on the market but the patent is under supervision of WHO (5).

Nifurtimox (Lampitâ, Bayer), a product used in the treatment of Chagas disease, has only been tested empirically in HAT with contradictory results (4,6,7). This is a cheap drug, which is easy to administer (orally) but not registered for use in HAT. The type and frequency of side effects are poorly documented.

The available therapeutic spectrum for the treatment of late-stage HAT is therefore limited. Furthermore, the availability of the 3 drugs listed here is only guaranteed in the medium-term. Finally, signs of resistance to melarsoprol are beginning to appear in several areas (8,9).

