## Results and side effects of treatment with melarsoprol

In the late-stage disease, the cure rate after treatment with melarsoprol is estimated to be greater than 95% (10,11,14). The principal risk is that of reactive encephalopathy (5.9% of cases treated with melarsoprol in a series of 1083 patients in Zaire (15), with a high mortality rate (67.2% in the same series). In an Ivory Coast series with 350 patients (6), arsenical treatment was associated with minor side effects, such as isolated febrile episodes, pruriginous rashes and subcutaneous cellulitis, sometimes followed by necrosis at the injection site, in 11.4, 4.6 and 2.8% of cases, respectively.

MSF data from Adjumani in Northern Uganda provide the following figures: among 3110 late-stage patients treated with melarsoprol, 567 (18.2%) patients suffered side effects, including 194 (6.2%) cases of reactive encephalopathy. The lethality observed during treatment was 5.5% (170/3110). The lethality of reactive encephalopathies was 51.5% (100/194). The median duration of hospitalisation was 25 days (unpublished MSF data).

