**3.4. Study duration**

If a treatment centre treats about 500 late-stage patients annually, allowing for the inclusion criteria, which restrict the potential recruitment, it may be estimated that patient recruitment to the study will be completed within a maximum of 12 months. As the patients are followed up subsequently for 24 months, the total study duration is estimated at 36 months.

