## Blind

The modes of administration of melarsoprol (direct IV), nifurtimox (orally) and eflornithine
(2-hour infusion) are different. A blind study is therefore not readily feasible under field conditions.

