## Side effects

In case of any side effect, the event will be recorded. The decision to withhold or to resume treatment will be left to the clinician in charge. Analysis will be done on an intention to treat basis.

The following definitions will be used for recording some of the side effects :

- Reactive encephalopathy: onset of a sudden or rapidly progressive episode of coma in a patient during treatment (Glasgow score less than or equal to 8) or status epilepticus.
- Arsobal reaction: tachycardia (pulse > 100 or 140 in children under 12 years of age), with fever > 38°C and conjunctival hyperaemia.
- Diabetes mellitus: fasting blood glucose greater than or equal to 1.3 g/l, associated with glycosuria.
- Cardiomyopathy: occurrence of an arrhythmia during treatment in a patient previously free from cardiovascular symptoms.
- Enteritis: occurrence of a diarrhoeic syndrome during treatment (three or more liquid stools per 24 hours, for three consecutive days or more) resistant to oral rehydration.

In case of occurrence of any manifestation that could lead to suspect imminent encephalopathy (severe headaches, conjunctival hyperaemia, high fever without a focus of infection or malaria parasites, isolated convulsion, behavioural disorders, etc.) the decision to withhold or to resume the treatment will be at the clinician’s discretion in accordance with the practices of the treatment centre.

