## Early stopping rules

Every hundred patients included, the three treatment groups will be compared regarding :

- the lethality,
- the proportion of therapeutic failures at the end of hospitalisation, defined by the presence of trypanosomes in the CSF and/or the blood,
- the frequency of occurrence of serious adverse reactions

If the proportion of one of these events is significantly higher in one treatment group as compared to the other groups, the recruitment in this group will be stopped.

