**3.8. Analysis**

This will be an "intention-to-treat" analysis. The treatment groups will be compared pair-wise.

The first outcome variable is the proportion of therapeutic failures in each treatment group.

The second outcome variable is the proportion of side effects occurring in each group.

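### Deaths of unknown cause are dropped from the primary analysis and censored as if unrelated, although the trial is open and declared intention-to-treat

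*Protocol*

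**What the plan says.** Protocol section 3.7, under Deaths, sorts deaths during the two years of follow-up into likely, unlikely or unknown causality, with respect to treatment and to trypanosomiasis. Likely deaths are failures. The other two categories share one rule: they "will be censored for the survival analysis and excluded from the primary end-point analysis".

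The surrounding text bears on this as follows:

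- Section 3.6, under Side effects: "Analysis will be done on an intention to treat basis". Section 3.8 declares the same principle for the trial's analysis.
- Section 3.6, under Blind: "A blind study is therefore not readily feasible under field conditions". Section 3.1 calls the design open.
- Introduction: "HAT, which is consistently fatal in the absence of treatment".
- Section 3.8 names three outcomes. The first is the proportion of therapeutic failures. For the next, "The second outcome variable is the proportion of side effects occurring in each group". The third is 24-month survival without signs of infestation, in which the Deaths rule censors unknown-cause deaths.
- Section 3.8, under Multivariate analysis, judges equivalence by whether the upper limit of a 90% interval for the difference between two groups stays below 10%.

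**The concern.** The label unknown means that a link to treatment or disease could be neither established nor ruled out. The protocol nevertheless handles it in the same way as a death judged unrelated. In a disease that is fatal when it persists, an unexplained death after treatment may be an undetected relapse, which is the event the trial sets out to count. Censoring it assumes that the patient's later risk of failure was the same as that of the survivors.

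The rule also removes randomised patients because of something that happens after randomisation, which is not intention-to-treat. Because the trial is open, the judgement is made by people who may know the arm.

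The equivalence verdict is at stake. If unexplained deaths are more frequent in the arm that is really worse, or are more often labelled unknown there, leaving them out lowers that arm's failure rate and narrows the apparent difference.

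**Working it through.** **Inputs.** From section 3.3: cure rate 95%, maximum difference 10%, one-sided alpha 5%, power 80%, equal allocation, 10% drop-out. From section 3.8: one-sided 95% upper limit compared with 10%. Assumed, because the protocol gives no figure: the rate of unknown-cause death in each arm.

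**1. The plan's own sample size.** For 95% against 85%, one-sided 5%, 80% power:

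n' = [1.645 × √(2 × 0.90 × 0.10) + 0.842 × √(0.95 × 0.05 + 0.85 × 0.15)]² / 0.10² = (0.698 + 0.352)² / 0.01 = 110.2.

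With the continuity correction, n = (n'/4) × [1 + √(1 + 4/(n' × 0.10))]² = 129.5, so 130. Then 130/0.9 = 144.4, so 145. Both stated figures reproduce and are not in dispute. The steps below use 145 per arm and ignore drop-out.

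**2. How the rule acts on one result.** Upper limit = p1 − p2 + 1.645 × √[p1(1 − p1)/n1 + p2(1 − p2)/n2]. Suppose one arm has 12 failures and 3 unknown-cause deaths, and the other has 7 failures and no such deaths.

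- Deaths excluded: 12/142 against 7/145. Difference 3.6%, standard error 2.94%, upper limit 8.5%: equivalent.
- Deaths counted: 15/145 against 7/145. Difference 5.5%, standard error 3.09%, upper limit 10.6%: not equivalent.

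The window for such a reversal is narrow. With 3 deaths against none and 7 failures in the other arm:

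| Failures in first arm | Limit, deaths excluded | Limit, deaths counted |
|---|---|---|
| 7 | 4.3% | 6.6% |
| 11 | 7.6% | 9.8% |
| 12 | 8.5% | 10.6% |
| 13 | 9.3% | 11.4% |
| 14 | 10.1% | 12.2% |

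Only 12 or 13 failures change the verdict. Starting from 7 failures in each arm, it takes 8 unknown-cause deaths against none (15/145 against 7/145, 10.6%); 7 against none gives 9.8%.

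**3. Chance of declaring equivalence at the limit.** Let the true failure rates, with unknown-cause deaths counted, be 15% and 5%. If a share u of an arm dies of unknown cause and is excluded, the failure rate among those left is (p − u)/(1 − u). The probability that the upper limit is below 10%, from exact binomial sums:

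| Unknown-cause deaths, worse / other arm | Rates left in the analysis | Apparent difference | Chance of declaring equivalence |
|---|---|---|---|
| counted | 15.0% / 5.0% | 10.0 points | 5.6% |
| 1% / 0 | 14.1% / 5.0% | 9.1 points | 9% |
| 2% / 0 | 13.3% / 5.0% | 8.3 points | 14% |
| 3% / 0 | 12.4% / 5.0% | 7.4 points | 21% |
| 2% / 2% | 13.3% / 3.1% | 10.2 points | 5.5% |
| 1% / 3% | 14.1% / 2.1% | 12.1 points | 1.5% |

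**4. What the interim looks see.** Section 3.6 provides that "Every hundred patients included, the three treatment groups will be compared regarding" lethality, among other things, and section 3.4 expects that "patient recruitment to the study will be completed within a maximum of 12 months". If 435 patients enter evenly over 12 months, the 400th enters at 400/435 × 12 = 11.0 months, when mean follow-up is about 5.5 months. The follow-up time seen by then is 400 × 5.52/(435 × 24) = 21% of the total, so about 79% is still to come.

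**The case against.** The strongest objection is that the gap is small and its direction unknown. Much of this stands.

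- Section 3.7 looks for relapse by lumbar puncture at 6, 12 and 24 months, with unscheduled visits and active tracing. A failure found at any control visit counts, so a patient found relapsed who later dies is not lost.
- Likely related deaths are failures, and lethality is compared at the recruitment looks. A reader might infer that the trial disregards mortality. It does not. What escapes is the unexplained death without an earlier detected failure, mostly after the last look.
- A reader might also infer that the rule favours equivalence. The reversed case in the working shows that it can equally work against it.
- Section 1.1 reports 170 deaths among 3110 patients on melarsoprol, 100 of them from encephalopathy. It is tempting to take the other 70 (2.25% of patients) as a rate of unexplained death. The documents do not support that. These deaths occurred during treatment, on melarsoprol alone, and carry no causality label, whereas the Deaths rule concerns the two years of follow-up.
- The absence of causality criteria and of a masked assessor could be read as a defect in itself. Such detail is commonly left to an analysis plan, which is not at hand, and is not held against the protocol here.
- Censoring deaths judged unrelated is an ordinary choice for a disease-specific outcome. That defends the unlikely category but not the unknown one, and even for the unlikely category it remains an exception to intention-to-treat that should be named as such.

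**Conclusion.** The point holds as a conflict between a stated rule and a stated principle. An analysis plan that followed the Deaths rule would carry the conflict forward. It should be corrected, but it does not show that the trial's conclusion would be wrong.

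The size depends on a rate that the protocol does not give. Under the assumed rates in the working, the nominal 5.6% error at the limit becomes anything from 1.5% to 21%, and with balanced deaths it hardly moves. Those figures define every unknown-cause death as a true failure, which is the cautious reading and not an established fact. A verdict resting on two or three such deaths is possible, but only for results already close to the 10% limit.

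**What to change.** Replace the third bullet under Deaths in section 3.7 with:

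*Deaths of unknown cause count as treatment failures in the first outcome and as events in the survival analysis. Deaths considered unlikely to be related to both treatment and trypanosomiasis are censored in the survival analysis and left out of the main analysis of the first outcome, as a stated exception to intention-to-treat. A sensitivity analysis in all randomised patients counts every death as a failure. Equivalence is described as robust only if both analyses meet the 10% limit.*

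Add to section 3.8 a pair-wise comparison of death from any cause, over treatment and the 24 months of follow-up.

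No new data are needed, because deaths and their causality are already to be recorded. The main analysis still leaves out deaths judged unlikely to be related, so the conflict with intention-to-treat is declared and tested, not removed.

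The price is that some unrelated deaths will count as failures. Probability of meeting the 10% limit when both arms have the same failure rate (exact binomial):

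| Points added to the 5% failure rate in both arms | 145 per arm | 130 per arm |
|---|---|---|
| 0 | 98.5% | 97% |
| 1 | 97% | 95% |
| 2 | 95% | 93% |
| 3 | 93% | 90% |
| 5 | 88% | 85% |

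All of these remain above the planned 80%.

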**3.8. Analysis**

This will be an "intention-to-treat" analysis. The treatment groups will be compared pair-wise.

The first outcome variable is the proportion of therapeutic failures in each treatment group.

The second outcome variable is the proportion of side effects occurring in each group.

## Survival analysis

The third outcome variable will be the duration of survival without signs of parasitic infestation for 24 months after treatment. The survival curves for each group will be compared using the Kaplan Meier technique, which includes drop outs, and the log rank test.

## Multivariate analysis

Certain clinical and laboratory variables might be confounding factors, which must be taken into account during the analysis. Cox’s model (proportional hazard) will be used to obtain an estimate of the relative risk adjusted for these variables.

In an equivalence study, the point of interest is the difference observed between the two groups, assuming a 90% confidence interval (or an upper limit of 95%) around this difference (with a one-tailed test):

- If the upper limit is above 10%, the null hypothesis that there is a difference between the 2 groups cannot be rejected. If B is compared with A, it will be concluded that B is superior to A (at the 20% level).
- If the upper limit is below 0%, it will be concluded that A is superior to B (at the 20% level).
- Finally, if the upper limit is between 0 and 10%, the null hypothesis may be rejected and the alternative hypothesis accepted that the 2 groups A and B are equivalent (at the 5% level).

In the same way, for the analysis of survival, a 90% confidence interval (or an upper limit of 95%) is set around the relative hazard:

- If the upper limit is above a relative hazard of 1.12 (0.95/0.85) (i.e. 1.12 times more risk of treatment failure during the 24 months following treatment in one group than in the other), the null hypothesis that there is a difference between the 2 groups cannot be rejected.
- If the upper limit is below 1.0, it will be concluded that A is superior to B (at the 20% level).
- Finally, if the upper limit is between 1.0 and 1.12, the null hypothesis may be rejected and the alternative hypothesis accepted that the two groups A and B are equivalent (at the 5% level).

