## Alternative hypothesis

The difference in the cure rates between 2 groups obtained during the treatment of patients in the meningo-encephalitic phase is less than or equal to 10%.

If the observed difference in cure rates between the 2 groups is less than 10%, the null hypothesis will be rejected and the two treatments will be considered equivalent. The risk of error will then be 5% (alpha error) because if the difference in actual cure rates between the 2 treatments is greater than 10%, there is a 95% chance of demonstrating it (alpha error). Conversely, if the observed difference in the observed cure rates between the two groups is greater than 10%, the null hypothesis will not be rejected and the 2 treatments will be considered different, at a beta error set at 20%. The allocation ratio will be uniform (1 patient in group A to 1 patient in group B to 1 patient in group C).

Assuming a 95% cure rate, a maximum difference in cure rates between the groups of 10%, an identical drop-out rate in the 3 groups, an alpha error of 5% (one-sided test) and a power of 80%, this yields a sample size of 130 patients to be included in each group, i.e. 390 patients in the study. Allowing for a 10% drop-out rate, a final figure of 145 patients per group is obtained, i.e. 435 patients in total.

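### An upper limit above 10% is read as proof that B is superior to A, although the interval may include zero and no inconclusive outcome exists

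*Protocol*

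**What the plan says.** Section 3.8 of the Protocol, under Multivariate analysis, puts a 90% confidence interval around the difference between two groups and decides by its upper limit.

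- First bullet: "If the upper limit is above 10%, the null hypothesis that there is a difference between the 2 groups cannot be rejected". The next sentence draws the conclusion: "If B is compared with A, it will be concluded that B is superior to A (at the 20% level".
- Second bullet: an upper limit below 0% means A is superior.
- Third bullet: an upper limit between 0 and 10% means the two groups are equivalent.

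These bullets agree with each other only if the difference is cure in B minus cure in A, so I read it that way.

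The relative-hazard rule that follows has the same shape, but its first bullet stops at non-rejection and names no winner.

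Section 3.3 (Alternative hypothesis) decides on the observed difference instead. Below 10% the treatments are equivalent. Above 10%, "the null hypothesis will not be rejected and the 2 treatments will be considered different, at a beta error set at 20" per cent.

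**The concern.** An upper limit above 10% says only that an advantage of more than 10 points for B has not been ruled out. It does not show that B is better. The rule turns a failure to show equivalence into a positive finding, and the three bullets between them leave no room for an inconclusive result.

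The rule is also lopsided. A wins only when the interval excludes zero; B wins whenever the interval is wide enough to reach past 10%. Which regimen benefits therefore depends on the label it is given in the comparison. Anything that widens the interval (more failures, more losses, an arm closed early) makes a claim for B more likely. At stake is a recommendation of one regimen over another, in a fatal disease, without evidence of a difference.

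**Working it through.** **Inputs.** From section 3.3: "Assuming a 95% cure rate, a maximum difference in cure rates between the groups of 10" per cent, and "an alpha error of 5% (one-sided test) and a power of 80" per cent. From section 3.8: a 90% interval, so z = 1.645.

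**The plan's own figure.** For 95% v 85% cure, one-sided 5%, 80% power:

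- n0 = [1.645·√(2·0.90·0.10) + 0.842·√(0.95·0.05 + 0.85·0.15)]² / 0.10² = 110.2, so 111 uncorrected.
- With continuity correction: n = (n0/4)·[1 + √(1 + 4/(n0·0.10))]² = 129.5, so 130.
- 130/0.90 = 144.4, so 145 per group and 435 in all.

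This reproduces the 130 and the 145. I use 130 evaluable per arm below.

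**Chance of the B-superior conclusion when the arms are identical.** With common cure rate p, SE = √(2p(1-p)/130), and P(upper limit > 0.10) ≈ 1 - Φ(0.10/SE - 1.645).

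- p = 0.95: SE = 0.0270; 1 - Φ(2.05) = 2.0%.
- p = 0.90: SE = 0.0372; 1 - Φ(1.04) = 14.9%.
- p = 0.85: SE = 0.0443; 1 - Φ(0.61) = 27.0%.
- p = 0.75: SE = 0.0537; 1 - Φ(0.22) = 41.4%.

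Exact enumeration of the two binomials, with the unpooled Wald 90% interval, one comparison:

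| Cure, both arms | B declared superior | of which interval includes zero | of which interval excludes zero | A declared superior |
|---|---|---|---|---|
| 95% | 2.6% | 0.3% | 2.4% | 5.6% |
| 90% | 15.0% | 9.9% | 5.2% | 5.2% |
| 85% | 26.8% | 21.7% | 5.0% | 5.0% |
| 75% | 41.3% | 36.2% | 5.1% | 5.1% |
| 70% | 45.7% | 40.7% | 5.0% | 5.0% |

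The B-superior rate passes 20% just below 88% cure. If A is truly 2 points better (76% v 74%), B is still declared superior in 28%.

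**One data set under both rules.** Take 36/130 failures in A and 33/130 in B.

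- Difference in cure = 3/130 = 2.3 points.
- SE = √(0.723·0.277/130 + 0.746·0.254/130) = 0.0547, and 1.645·SE = 9.0 points.
- Interval: -6.7% to +11.3%.

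Section 3.8 declares B superior. Section 3.3 sees an observed difference below 10% and declares the treatments equivalent.

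**Section 3.3 taken alone.** With identical arms, P(observed difference above 10% in either direction) is 0.02% at 95% cure, 1.9% at 85% and 5.3% at 75%. In essentially none of these cases does the 90% interval include zero.

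**An arm closed early (illustration).** Section 3.6 compares the arms every hundred patients and may stop recruitment to one. Assume the arm entered as B stops at about 100/3 = 33 and is compared with 130. Identical arms then give a B-superior conclusion in 12% at 95% cure and 47% at 90%. This shows the loss of precision only; it does not model why the arm was closed.

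**After the fix, 130 per arm.** A false B-superior claim needs the lower limit above zero: 2.4% at 95% cure, 5.0% at 85%, 5.1% at 75%. In the same enumeration the inconclusive outcome takes 0.5% of comparisons at 95% cure, 43% at 85% and 72% at 75%.

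**The case against.** The best defence is that the trial was planned at 95% cure. There the B-superior error is 2.6%, below the 5.6% for A, and the interval includes zero in only 0.3%. That stands: under the planning assumption the numerical effect is small.

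A reader might infer that identical arms yield a superiority claim in up to 41% of trials. The Protocol does not support that.

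- The 41% needs 75% cure in both arms. Section 1.2 reports about 25% failures in Arua for melarsoprol alone, and nothing assumes that rate for the combinations; group C contains no melarsoprol.
- It applies to one pairwise comparison, not to a whole trial with three.
- It is not a ceiling, since the rate reaches 46% at 70% cure.

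A reader might also take section 3.3 as a second instance of the same error. It is not: its trigger is an observed difference above 10%, and results that meet it exclude zero almost without exception. It is a conflicting rule. Nor does the relative-hazard rule share the defect, because its matching branch claims no superiority.

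The label of a 20% level does not rescue the rule. The error rate depends on the cure rate and exceeds 20% once cure falls just below 88%, so the rule does not control error at 20%. A separate analysis plan, not seen here, could not simply fill a gap either, because the Protocol itself fixes the rule.

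**Conclusion.** The first bullet for the difference is wrong as written. It concludes superiority from a failure to show equivalence, without consulting the lower limit. That holds whatever the cure rate.

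The size depends on the cure rate: about 3% of comparisons at 95%, 15% at 90%, 27% at 85% and 41% at 75%. These figures assume identical arms, 130 evaluable per arm, one comparison and a Wald interval. Cure below 95% is plausible at a site with documented melarsoprol resistance, when two of the three arms contain melarsoprol and deaths judged likely due to treatment or disease count as failures. How far below is unknown. Early closure of an arm raises the figures further.

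Separately, sections 3.3 and 3.8 give two decision rules that can return different conclusions from the same data.

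**What to change.** In section 3.8, replace the superiority sentence of the first bullet with mutually exclusive outcomes, and bring the other two bullets into line:

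1. Equivalent if the whole 90% interval lies within -10% to +10%. If it also excludes zero, report that separately; the classification stays equivalent.
2. Otherwise, one arm superior only if the interval excludes zero in that arm's favour.
3. Otherwise inconclusive: neither equivalence nor superiority shown.

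Rewrite the decision sentences of section 3.3 to refer to this interval rule instead of the observed difference. In the relative-hazard rule, only label the first branch inconclusive unless the interval excludes 1.0.

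The cost is wording in two sections, with no added patients or data. The sponsor must accept that if cure falls well below 95%, many comparisons will be reported as inconclusive. With 130 per arm, false claims for B then stay at about 5% or less per comparison. That figure does not carry over to a very small closed arm, where Wald limits are unreliable.

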**3. Methods**

**3.1. Study design**

Open, randomised, clinical equivalence trial

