**3.3. Sample size**

## Null hypothesis

The difference in the cure rates between 2 groups obtained during the treatment of patients in the meningo-encephalitic phase is greater than 10%.

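### Equivalence is judged on the upper confidence limit alone, so the 5% false-equivalence risk holds in one direction only and the order of subtraction can change the verdict

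*Protocol*

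**What the plan says.** Section 3.1 describes the study as "Open, randomised, clinical equivalence trial". Under Null hypothesis (section 3.3) the null reads "The difference in the cure rates between 2 groups obtained during the treatment of patients in the meningo-encephalitic phase is greater than 10" per cent. The alternative is that the difference in the same "phase is less than or equal to 10" per cent. Neither names a direction. Section 3.8 adds "The treatment groups will be compared pair-wise", and no arm is designated as control.

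The sample size assumes "an alpha error of 5% (one-sided test) and a power of 80" per cent, with 95% cure and a 10-point margin. It gives 130 per group, or 145 after allowing for 10% drop-out.

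The decision rule stands under Multivariate analysis in section 3.8. A 90% interval is formed, but only its upper limit is used:

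- Above 10%: the null is not rejected and, for B compared with A, B is called superior.
- Below 0%: A is called superior.
- In between, equivalence of the pair is claimed with a 5% error: "if the upper limit is between 0 and 10%, the null hypothesis may be rejected and the alternative hypothesis accepted that the 2 groups".

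The relative-hazard rule has the same one-limit form: "if the upper limit is between 1.0 and 1.12, the null hypothesis may be rejected".

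**The concern.** One confidence limit can rule out a large difference in one direction only. That suits non-inferiority to a named control. It does not test a symmetric hypothesis about arms that have no order. Nothing in the rule prevents an equivalence verdict when the lower limit is beyond -10%, that is, when the data still allow one arm to be more than 10 points worse.

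Two things are at stake for the first outcome. The stated 5% risk of false equivalence is not met in the unguarded direction. The verdict can also depend on a choice the protocol leaves open: which arm is subtracted from which, for each of three pairs. The hypotheses speak of cure and section 3.8 names failures as the first outcome; switching between them also reverses the sign.

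**Working it through.** **1. The protocol's own sample size.** Inputs (section 3.3): 95% versus 85%, one-sided 5% (z = 1.645), power 80% (z = 0.842), mean rate 0.90.

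- n = [1.645·√(2·0.90·0.10) + 0.842·√(0.95·0.05 + 0.85·0.15)]² / 0.10² = 110.2.
- With continuity correction: (110.2/4)·[1 + √(1 + 4/(110.2·0.10))]² = 129.5, rounded up to 130.
- 130/0.90 = 144.4, rounded up to 145.

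Both stated figures are reproduced.

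**2. One data set, two verdicts.** The protocol names no interval method, so Wald limits are assumed. Take B = 116/130 (89.2%) and A = 123/130 (94.6%).

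- Difference B - A = -5.4 points. SE = √(0.892·0.108/130 + 0.946·0.054/130) = 0.0336. Half-width = 1.645·0.0336 = 5.5 points.
- B - A: -10.9 to +0.15. The upper limit is between 0 and 10, so the verdict is equivalent, although the lower limit is beyond -10.
- A - B: -0.15 to +10.9. The upper limit is above 10, so the arms are not equivalent, and the arm with the higher cure rate is called superior.

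**3. Probability of an equivalence verdict at a true gap.** Let the first arm of the subtraction be the worse one, with true rate p, and the other have true rate q. Sum Bin(x; n, p)·Bin(y; n, q) over all outcomes (x, y) with 0 ≤ upper limit ≤ 10%.

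| True rates | n per group | Rule as written | Both limits within ±10% |
|---|---|---|---|
| 85% vs 95% | 130 | 12.6% | 5.6% |
| 85% vs 95% | 145 | 9.5% | 5.6% |
| 84% vs 95% | 130 | 8.5% | 3.2% |
| 80% vs 90% (assumed) | 130 | 26% | 5.2% |
| 75% vs 85% (assumed) | 130 | 34% | 4.3% |

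Hand check of the first row by normal approximation: SE = √(0.175/130) = 0.0367 and half-width 0.0603. P(upper limit ≥ 0) = 1 - Φ((0.10 - 0.0603)/0.0367) = 1 - Φ(1.08) = 14%, close to the exact 12.6%. In the guarded order of subtraction, the written rule gives 5.6% at 95% versus 85%. The small excess over 5% comes from the Wald interval.

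**4. Observed gaps.** At an observed 85% versus 95% with 130 per group the half-width is 6.0 points, so the upper limit is about -4% and the below-0% branch applies. Going through all outcomes at 130 and at 145 per group, none with an observed gap above 10 points is called equivalent.

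**5. Power with both limits.** At 95% cure in both arms:

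- 80% power needs (1.645 + 1.282)²·2·0.95·0.05/0.10² = 81.4, so 82 per arm.
- Exact power is 94.8% at 130 and 96.9% at 145.

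**6. The hazard rule.**

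- The limit 1.12 is 0.95/0.85, a ratio of cure proportions. The hazard ratio implied by 85% versus 95% cure is ln(0.85)/ln(0.95) = 3.2.
- Expected failures per pair at 95% cure: 2·130·0.05 = 13. The 90% interval then spans a factor of about exp(1.645·√(4/13)) = 2.5 each way.
- For the interval to fit between 1/1.12 and 1.12, about 4·(1.645/ln 1.12)² = 843 events per pair are needed, against 435 patients in the whole trial.

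**The case against.** It can be said that the protocol is openly one-tailed and that its below-0% branch removes the worst cases. The second part stands. A reader might infer that arms observed to differ by more than 10 points could be called equivalent; step 4 shows that this does not happen at the planned size. The defect concerns true differences and differences that the interval still allows. The one-tailed label does not rescue the rule, because the hypotheses are non-directional and no arm is the reference.

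A reader might also take the 26% and 34% as the expected error. They rest on cure rates below the planned 95%. The nearest support, about 25% failures at Arua (section 1.2), concerns melarsoprol alone, not these combinations. At the planned rate the ignored lower limit adds about 7 points at 130 per group (12.6 - 5.6) and about 4 at 145.

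Nor should all order dependence be blamed on the missing lower limit. For identical arms at 95% cure and 130 per group, the two orders disagree in 6.9% of trials. Of this, 6.4 points come from the below-0% branch, which has no mirror image, and only 0.5 from the ignored lower limit. Adding a lower limit to the third branch alone would therefore leave the verdict dependent on order.

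A statistical analysis plan could add detail, but the protocol itself already fixes this rule.

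**Conclusion.** The concern holds for the risk-difference rule. The rule does not test the symmetric hypothesis stated in section 3.3. Its 5% risk of false equivalence applies in one direction only; in the other, at the planned 95% versus 85%, it is 12.6% with 130 per group and 9.5% with 145, against about 5.6% with both limits. The same data can give opposite verdicts, depending on the order of subtraction or on whether cure or failure is used.

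The sizes assume Wald 90% limits; the larger figures also assume lower cure rates. The hazard rule shares the one-limit form, and a reader might infer that it needs the matching reciprocal bound. The protocol's own numbers do not support that: 1.12 is not a hazard-ratio margin, and no interval of that width is attainable with about 13 expected failures per pair.

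**What to change.** Rewrite all three risk-difference branches in section 3.8 so that they read the same for either arm, and state whether cure or failure is subtracted:

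- **Equivalent** only if the whole 90% interval lies within -10% to +10% (two one-sided 5% tests).
- **One arm superior** only if the interval excludes 0, in the same terms for either arm. State which conclusion takes precedence when both conditions hold, as with an interval of -9% to -1%.
- **Otherwise inconclusive.** Draw no superiority conclusion from an upper limit above 10%.

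Under Alternative hypothesis in section 3.3, describe the test as two one-sided tests. Do not add a reciprocal 1.12 bound to the hazard rule. Base the equivalence verdict on the risk difference and report the hazard ratio with its interval as supportive.

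The cost is a rewritten paragraph in section 3.8 and a phrase in section 3.3. No patients are added: power at 95% cure in both arms is about 95% with 130 per group and 97% with 145, above the stated 80%. If superiority is given precedence, subtract the 6.4 points of overlap at 130 per group, which leaves about 88%.

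The downside is that equivalence becomes harder to claim if cure rates are lower. At an assumed 85% in both arms and 130 per group, SE = √(2·0.85·0.15/130) = 0.0443, and power is about 2Φ(0.10/0.0443 - 1.645) - 1 = 46%.
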